The hospitalisation rate consists of two elements: the number of hospitalisations and the period (in years) over which patients are followed up. We conducted simulations using the paramtest software package [76], computing 10′000 iterations of the chosen parameters. Based on the USB’s available data, we set the hospitalization events per patient year to 1.56. The study’s observation period is 15 months (1.25 years). We determined the minimum sample size using the inverse of the effect size in Schenkel et al. [6], i.e., 1.79 [1.31–2.43]. Following Olivier et al.’s guidance [77], we aimed for the upper bound of a small effect size. The simulation is based on a binomial distribution with a shape parameter of 4. Assuming an α level of 0.05, a power of 80% and an effect size of 1.79, a minimum sample size of 52 patients (26 per group) was determined. Based on a refusal rate of 10% and a 15% drop out rate, then, we will aim to recruit a total of 80 patients (40 per group). Considering that approximately 70 adults per year receive *both alloSCT and follow-up* at USB, recruitment will take a minimum of 16 months.

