#### Analysis

Statistical analyses will be conducted at the University of Basel’s Institute of Nursing Science using the R software package [96]. Data cleaning will include systematic screening for out-of-range values and data inconsistencies. Multiple imputations will be considered for missing data. Descriptive statistics will be applied as appropriate for all variables.
***Aim 1a:*** To determine whether hospitalisation rates (primary outcome) are reduced via the SMILe-ICM’s implementation, we will analyse any differences between IG and UCG rates by applying generalised linear mixed models (GLMM) [97]. The relevant variables (i.e., time, study group, and group x time interaction) will be entered into the models. Our targeted test statistic is the rate ratio by unconditional maximum likelihood estimation (Wald) as described by Rothman et al. [98] and implemented in epitools [99]. We will conduct intention-to-treat and per-protocol analysis. Two-sided significance will be set at 0.05. To analyze the target secondary outcomes over the course of time, descriptive analyses will be carried out and GLMM will be used to determine differences between the IG and UCG. Cost data will be collected and analysed quarterly. Overall survival will be analysed using the Kaplan-Meier method and the log-rank test. To analyse QALY, we will use the EQ-5D-5L**©** value set for Germany. The electronically compiled dosing history will be analysed using by applying GLMM, which account for dependence among observations from a single patient over time. The resulting estimates will be expressed as odds ratios (ORs) [100].
***Aim 1b:*** To test a potential wane-out effect of the SMILe-ICM’s intervention effect over 3 months’ post-intervention follow-up, differences between the IG and the UCG will be determined by applying GLMM. This approach allows calculation of the main group and time effects, and of group-by-time interaction effects. Two-sided significance will be set at 0.05.

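### The primary analysis names both a GLMM and a crude Wald rate ratio without saying which decides; if the Wald ratio decides, its type I error under the plan's apparent shape parameter is about 9–11%, not 5%

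*Protocol article*

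**What the plan says.** Protocol article, Analysis, Aim 1a. On the primary outcome the text first says "we will analyse any differences between IG and UCG rates by applying generalised linear mixed models (GLMM"), and continues: "The relevant variables (i.e., time, study group, and group x time interaction) will be entered into the models". The next sentence reads "Our targeted test statistic is the rate ratio by unconditional maximum likelihood estimation (Wald"), and names the R package epitools as its implementation. Two-sided significance is set at 0.05. No sentence ranks the two procedures, and no dispersion correction is given for the rate ratio.

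Protocol article, Sample size determination for aim 1. "The simulation is based on a binomial distribution with a shape parameter of 4". Further inputs: "we set the hospitalization events per patient year to 1.56"; "The study’s observation period is 15 months (1.25 years"); a rate ratio of 1.79, taken as the inverse of the effect in a cited lung-transplant study; alpha 0.05; power 80%. The result is 26 per group, raised to 40 per group for refusal (10%) and dropout (15%).

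Table 3 defines the primary outcome over a shorter window than the 15 months above: events after the initial discharge, within the first year after transplantation.

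**The concern.** The unconditional maximum-likelihood Wald ratio pools events and person-time within each arm and takes sqrt(1/a + 1/b) as the standard error of the log ratio, where a and b are total events. That is right only if all patients in an arm share one Poisson rate. Re-hospitalisations after allogeneic transplantation would be expected to cluster in some patients, and a shape parameter in the design simulation suggests that the authors allowed for this. If so, the test ignores a source of variation that the sample size assumes.

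This is the sole primary outcome. A test that rejects too often, with an interval that is too narrow, would overstate the evidence for the care model. Having two candidate primary p-values at one 0.05, with no stated order, also leaves room to choose after seeing the data.

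**Working it through.** **Inputs.** Rate 1.56 per patient-year, rate ratio 1.79, shape 4, two-sided 0.05, 26 per group minimum, 40 recruited per group (all from the sample-size text). 40 less 15% dropout is 34 analysed per group. Exposure per patient: 1.25 years (sample-size text); 1 year (Table 3 at its longest); about 0.93 years, which is (365 − 25)/365 using the average 25-day stay after transplantation in Context and targeted sites; and 0.5 years, the rough care time per patient given in the sample-size text.

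**Assumption.** An ordinary binomial has no shape parameter, so I read the distribution as negative binomial with size k = 4 and variance μ + μ²/4, where μ is the expected count per patient.

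**Reproducing the stated 26 per group.** Take 1.56 against 1.56 × 1.79 = 2.79 per year, 1 year each, with the crude Wald test applied to negative binomial counts.
- Poisson variance per patient: 1/2.79 + 1/1.56 = 0.999.
- Negative binomial variance: 0.999 + 2/4 = 1.499.
- (ln 1.79)² = 0.339.
- n = (1.960 × √0.999 + 0.842 × √1.499)² / 0.339 = 26.4 per group.
- Simulated power is 79.1% at 25 and about 80.5% at 26 per group.

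So 26 is the first size above 80%. This supports both the negative binomial reading and the crude Wald test as the design test. The match needs 1 year, not 1.25 (which gives about 86.5% at 26), and a higher rate of 2.79 rather than a fall from 1.56. A pure Poisson, one-sided calculation for 1.56 against 0.87 over 1.25 years also comes close (81.1%), but it contradicts both the two-sided test and the shape parameter.

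**Type I error of the crude Wald test.** With both arms at 1.56 per year the true variance exceeds the assumed one by the factor 1 + μ/4, so the error is approximately 2 × (1 − Φ(1.96/√(1 + μ/4))).

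| Exposure | μ | 1 + μ/4 | Formula | Simulated, 26–40 per group |
|---|---|---|---|---|
| 0.5 y | 0.78 | 1.195 | 7.3% | 6.7–7.0% |
| 0.93 y | 1.45 | 1.363 | 9.3% | 8.8–9.2% |
| 1 y | 1.56 | 1.390 | 9.6% | 9.1–9.5% |
| 1.25 y | 1.95 | 1.488 | 10.8% | 10.5–10.7% |

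More patients do not reduce the error. If both arms have the lower rate 1.56/1.79 = 0.87, it is about 7–8% over 1 to 1.25 years. Adding 2/(nk) to the variance, with n per group, brings it to 4.7–5.0% for 0.93 to 1.25 years. With pure Poisson data the crude test is also correct (4.5–4.9%).

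**Interval width.** For 1.56 against 0.87 over 1 year the Poisson variance is 1/1.56 + 1/0.87 = 1.79 and the negative binomial variance 2.29. A correct interval is √(2.29/1.79) = 1.13 times as wide on the log scale. Over 1.25 years the factor is √(1.93/1.43) = 1.16. In the reproducing scenario it is √(1.499/0.999) = 1.22.

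**Power with a dispersion-aware test (k taken as known).**
- 1.56 against 2.79, 1 year: about 68–69% at 26 per group, about 80% at 34, about 86% at 40. The minimum becomes (1.960 + 0.842)² × 1.499 / 0.339 = 34.7, so 35 per group.
- 1.56 as the usual-care rate falling to 0.87: at 34 per group about 59% (0.93 y), 62% (1 y) and 69% (1.25 y). About 53 (1 y) or 45 (1.25 y) per group would be needed for 80%.

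**The case against.** The strongest reply is that the GLMM comes first in the paragraph. If it has a patient random intercept and it decides, the error is near 5%, and the crude ratio is only a summary. Family, offset, time coding and random effects are details that an article may leave to the full protocol or analysis plan. This stands, and it makes the inflated error conditional. It does not remove the problem, because the text itself calls the crude ratio the target statistic and fixes its software and the significance level.

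Second, the article never says negative binomial or overdispersion. That stands too. Read literally as four binomial trials per patient, the crude test would be conservative (0.6–2.8%). The reproduction of 26 per group favours the negative binomial reading without proving it.

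A reader might go further and infer that the GLMM also fails, because with an interaction in the model its group coefficient refers to one reference interval and has little power. The document does not support this: it states no time coding, reference interval or tested coefficient. Under Aim 1b it says that the approach yields main group and time effects as well as the interaction. With centred time or a marginal contrast, an overall effect is available.

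**Conclusion.** The concern holds in conditional form. The article fixes two different procedures for its one primary outcome and leaves open which decides. If the crude Wald ratio decides, and counts are negative binomial with size 4, its type I error is about 9% in the Table 3 window and up to about 10.7% if all 15 months count, against a stated 5%. At 0.5 patient-years it is about 7%. The interval is too narrow under the same conditions.

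Two stronger statements are not supported. One is that the trial's type I error simply is 10%: that needs the Wald test to decide, the inferred shape and the longest exposure. The other is that neither analysis validly tests the hypothesis: a GLMM with a patient random effect and a specified overall contrast could do so.

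**What to change.** Name one primary analysis: negative binomial regression, or a Poisson GLMM with a patient random intercept. Include log person-time at risk as an offset, and report one overall group rate ratio with its 95% confidence interval. Either omit group-by-time from this model or prespecify the overall contrast. Keep group-by-time for Aim 1b, and label the crude Wald ratio descriptive. In the sample-size text, state the distribution by name and what the shape parameter means.

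The change needs no new data, but it is not wording alone. The interval widens (about 13–16% on the log scale for a fall from 1.56 to 0.87 over 1 to 1.25 years), and 26 per group no longer gives 80% power in the scenario that reproduces it. The minimum sample size and power should be restated for the chosen test, saying whether 1.56 is the usual-care rate and which exposure window applies. The planned 40 per group, 34 after dropout, gives about 80% under 1.56 against 2.79 but only about 59–69% if 1.56 falls to 0.87.

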**Primary Outcome**		
Re-hospitalisation rate	Number of events after the initial post-alloSCT discharge per patient in the first year post-alloSCT	EHR

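### The primary outcome has two unranked analyses, and the one named as the target statistic ignores the between-patient variation that the sample size most plausibly assumes

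*Protocol article*

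**What the plan says.** In the protocol article, Analysis, Aim 1a, the primary outcome is first given a mixed model: "we will analyse any differences between IG and UCG rates by applying generalised linear mixed models (GLMM", with time, group and their interaction. The section then states: "Our targeted test statistic is the rate ratio by unconditional maximum likelihood estimation (Wald", citing a textbook method "implemented in epitools". The level is fixed: "Two-sided significance will be set at 0.05". No sentence ranks the two analyses, and for the primary outcome neither a family nor a random effect is given for the GLMM.

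Under Sample size determination for aim 1, the counts are described thus: "The simulation is based on a binomial distribution with a shape parameter of 4". The planning rate is given as "we set the hospitalization events per patient year to 1.56" and the follow-up as "observation period is 15 months (1.25 years". Table 3 defines the primary outcome over a shorter window: "Number of events after the initial post-alloSCT discharge per patient in the first year post-alloSCT".

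**The concern.** The pooled Wald ratio treats every admission in an arm as an independent event at one common rate. If some patients are readmitted far more often than others, admissions cluster within patients, and the variance of the log rate ratio exceeds what the event totals suggest. The sizing appears to assume exactly this. A binomial has no shape parameter, whereas a negative binomial with size 4 is a usual way to describe overdispersed counts.

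The planning model and the named test would then contradict each other on the primary outcome. The p-value would be too small and the interval too narrow, in an unblinded trial whose result is meant to support scale-up. Enrolling more patients does not cure this.

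**Working it through.** **Inputs**
- Test (Analysis, Aim 1a): z = ln(RR) / √(1/A + 1/B), where A and B are the event totals per arm; two-sided 5%.
- Usual-care rate 1.56 per patient-year and rate ratio 1.79 (sample size section).
- Dispersion: shape 4, read as negative binomial size k = 4, so variance = μ(1 + μ/4). This reading is an assumption.
- Exposure: 1.25 years (sample size section); first year (Table 3); 340 days, which is the first year less the average 25-day initial stay (Context and targeted sites); 0.5 year (the figure used to derive the baseline rate).
- Patients per group: 26 minimum, 40 recruited, and 40 × 0.85 = 34 after 15% dropout.

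**Step 1. The plan's own figure.** Simulating shape-4 counts and applying the two-sided Wald test over 1.0 year, with 1.79 as an increase (1.56 against 1.56 × 1.79 = 2.79), gives 80.7% power at 26 per group, and 26 is the smallest size that reaches 80%. With the stated 1.25 years the power at 26 is 86.5% as an increase (minimum 21) or 68.3% as a reduction (1.56/1.79 = 0.87 per year; minimum 36). The match therefore needs 1.0 year and an increase, and it is not unique. Poisson counts with a one-sided test over 1.25 years and a reduction also give 81%, but that does not fit shape 4 or the two-sided level.

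**Step 2. Error under the null.** With n per group and mean count μ, the true variance of ln(RR) is about (2/n)(1/μ + 1/k). The Wald statistic uses (2/n)(1/μ). The ratio is 1 + μ/4, so the actual error is 2[1 − Φ(1.96/√(1 + μ/4))].

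| Exposure | μ = 1.56 × years | 1 + μ/4 | SE ratio | Error, formula | Error, simulated |
|---|---|---|---|---|---|
| 0.5 year | 0.78 | 1.20 | 1.09 | 7.3% | about 7% |
| 340 days | 1.45 | 1.36 | 1.17 | 9.3% | about 9% |
| 1.0 year | 1.56 | 1.39 | 1.18 | 9.6% | 9.3-9.5% |
| 1.25 years | 1.95 | 1.49 | 1.22 | 10.8% | 10.5-10.7% |

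The simulated values hardly change between 26 and 40 per group.

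**Step 3. Controls.** Truly Poisson counts over 1.0 and 1.25 years give 4.9-5.0% with the same code, so the excess comes from overdispersion and not from small samples. On shape-4 counts a patient-level robust variance gives 5.3-5.7%, and a fitted negative binomial Wald test gives 5.4-6.0%.

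**Step 4. Power at 26 per group with a valid variance (shape 4).**

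| Exposure, direction | Pooled Wald | Robust variance |
|---|---|---|
| 1.0 year, increase | 80.7% | 69% |
| 1.0 year, reduction | 59% | 51% |
| 1.25 years, increase | 86.5% | 75% |
| 1.25 years, reduction | 68% | 58% |

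At 34 per group over 1.0 year the robust test has about 80% (increase) or 63% (reduction). The formula n = (1.96 + 0.84)² (1/μ₀ + 1/μ₁ + 2/4) / (ln 1.79)² asks for 35 per group over 1.0 year as an increase: 7.85 × (0.641 + 0.358 + 0.5) / 0.339 = 34.7. As a reduction it asks for 53.

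**The case against.** The GLMM comes first and is tied to the purpose of Aim 1a. With a patient effect it would hold the error near 5%. For the dosing data the same section notes that such models handle dependence within a patient, so the authors know the problem. The family and random effect may well stand in an analysis plan that is not shown. This stands: a reader might infer that the Wald ratio is the decisive test, but the article does not say so. The reproduction of 26 per group does not prove it either, since it needs 1.0 year instead of the stated 1.25 and an increase where the hypothesis is a reduction.

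Two further limits stand. Shape 4 as a negative binomial is the most plausible reading but not the only conceivable one, and it is a planning value, not an observed dispersion. Also, the 10.5% figure belongs to 1.25 years, while Table 3 confines the primary outcome to the first year. Death or dropout lowers it a little more: 8.5-9.0% if 15-45% are lost by one year (an assumption).

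What does not stand is that this is only omitted detail. The article itself fixes a statistic and its software, and the epitools ratio is not an output of a GLMM. On the milder reading, two different tests are still stated for one primary outcome, and one of them is too liberal under the sizing assumption.

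**Conclusion.** The point holds in conditional form. The plan gives two analyses for its primary outcome without ranking them, and the one called the target statistic has a variance that conflicts with the most plausible reading of the sizing model. If that statistic decides, and shape 4 and 1.56 events per patient-year hold, its error is about 9% for the first-year outcome against a nominal 5%. The range is about 7% (mean exposure 0.5 year) to 10.5% (1.25 years).

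A reader might go further and say that the trial's real error is 9-11%, or twice the nominal level. The documents do not support that without conditions: the figure depends on which analysis decides, on the reading of shape 4, and on an exposure at the upper end that is longer than the outcome window.

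**What to change.** State one primary test: the overall group rate ratio from a patient-level negative binomial model with log time at risk as offset, or the overall group contrast of a GLMM with a patient random effect. Use a robust or small-sample variance. Report the epitools ratio descriptively, without a p-value. In the sample size section, change binomial to negative binomial if that is what was simulated.

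The change needs no new data, but it is not free. The standard error grows by about 17-22%, so the power in the sample size section should be restated under the corrected test, with the exposure and the direction of the 1.79 made explicit. At the 34 per group expected after dropout, power over one year is about 80% only if 1.79 is an increase over 1.56; for the hypothesised reduction it is about 63%.

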### The SMILe project: a two-phase implementation science project

Our project—the development/adaption, implementation and evaluation of an ICM in allogeneic stem cell transplantation facilitated by eHealth (SMIL*e-ICM*)—was designed to anticipate and address these methodological challenges to sustainably reengineer the follow-up care of alloSCT patients in a Swiss and German setting. AlloSCT patients are a growing group with complex care needs. In 2019, 43′581 patients across 51 countries received allogeneic stem cell transplants [42]. Despite improved long-term survival, mortality and re-hospitalisation rates remain substantial, especially in the first year post-alloSCT [43]. In particular, the first months post-alloSCT constitute the most complex phase in terms of life-threatening complications such as infections, acute graft-versus-host disease (aGvHD) and gastrointestinal complications [44–49]. Avoiding re-hospitalisations or at least shortening re-hospitalisation stays will require early detection and treatment of complications [50, 51]. To achieve that goal, alloSCT patients will need to self-manage complex therapeutic regimens; however, non-adherence is common [52–54]. While eHealth has been applied to deliver individual self-management support interventions [55, 56] or caregiver support [57] in alloSCT, the SMILe-ICM is novel. As a full-scale care model, it has the potential, when successfully implemented, to optimise care processes and ultimately improve this vulnerable group’s health outcomes.

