**Aim 1** has two parts**:**

**1a.** to evaluate the SMILe-ICM’s effectiveness in view of one primary outcome—re-hospitalisation rate—and seven secondary outcomes—total healthcare utilization costs, total length of inpatient re-hospitalizations, medication non-adherence, treatment burden, health-related quality of life (HRQL), quality-adjusted life year (QALY), acute and chronic GvHD incidence and grade, and overall survival rate. Regarding the primary outcome, we hypothesise that, compared to the usual-care/control group, patients receiving the SMILe-ICM will have a lower re-hospitalisation rate. As for the secondary outcome set, compared to the control group, we expect to see lower total healthcare utilization costs, shorter lengths of re-hospitalizations, lower medication non-adherence (implementation phase of adherence [67]), less treatment burden, better HRQL, higher quality-adjusted life years (QALY), and equal medical outcomes (acute and chronic GvHD incidence, overall survival).
**1b.** to extend objective **1a** by testing for a potential wane-out of the SMILe-ICM intervention effect in view of primary and secondary outcomes during the three-month post-intervention follow-up.
**Aim 2** is to evaluate the SMILe–ICM’s bundle of implementation strategies and assess acceptability, appropriateness, feasibility, and fidelity (implementation outcomes) as well to evaluate the implementation pathway (as viewed by patients and health care professionals).

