**Secondary outcomes**												
Healthcare utilisation costs	FIMA**©** (10 Items) [83]			**X**	**X**	**X**	**X**	**X**	**X**	**X**	**X**	**X**
	Swiss standardised unit costs [84, 85]			**X**	**X**	**X**	**X**	**X**	**X**	**X**	**X**	**X**
Length re-hospitalizations	FIMA**©** (10 Items) [83] Medical Records, CRF			**X**	**X**	**X**	**X**	**X**	**X**	**X**	**X**	**X**
Medication adherence (implementation & persistence dimension [67])	Electronic Monitoring: MEMS® Button [86]											
	BAASIS**©** (implementation 4 items; persistence: 1 item) [87]		**X**	**X**	**X**	**X**	**X**	**X**	**X**	**X**	**X**	**X**
Treatment burden	PETS**©** (60 items) [88]	**X**			**X**			**X**			**X**	
Health-related Quality of Life	EQ-5D-5L**©** (5 items) [89]	**X**	**X**	**X**	**X**	**X**	**X**	**X**	**X**	**X**	**X**	**X**
Quality-Adjusted Life Year (QALY)	EQ-5D-5L**©** (5 items) [89], value set for Germany EQ-VT v. 2.0 (116)	**X**	**X**	**X**	**X**	**X**	**X**	**X**	**X**	**X**	**X**	**X**
Incidence/grade chronic and acute GvHD	Medical record, CRF		**X**	**X**	**X**	**X**	**X**	**X**	**X**	**X**	**X**	
Overall survival rate	Medical record, CRF		**X**	**X**	**X**	**X**	**X**	**X**	**X**	**X**	**X**	**X**
Conditioning regimen	Medical record, CRF	**X**										
Donor match/type	Medical record, CRF	**X**										
Disease	Medical record, CRF	**X**										
Disease status at transplant	Medical record, CRF	**X**										
If death: Date and cause of death	Medical record, CRF		**X**	**X**	**X**	**X**	**X**	**X**	**X**	**X**	**X**	**X**
If relapse: Date of relapse	Medical record, CRF		**X**	**X**	**X**	**X**	**X**	**X**	**X**	**X**	**X**	**X**

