Treatment burden	German version of the PETS© self-reporting questionnaire [88]: nine multi-item domain scales, each measuring the burden of one aspect of chronic illness treatment on a 4- or 5-point Likert-type response scales regarding a 4-week recall time frame: medical information (7 items); medications (7 items); medical appointments (3 items); health monitoring (2 items); interpersonal challenges (4 items); health care expenses (5 items); difficulty with health care services (7 items); role/social activity limitations due to self-management (6 items); and physical/mental exhaustion due to self-management (5 items). Raw domain scores are transformed to a standardised 0-to-100 metric, with higher scores indicating greater treatment burden.	Paper survey (pat.)
Health-related Quality of Life	Measured using the EQ-5D-5L© [89], covering five dimensions (mobility, self-care, usual activities, pain/discomfort and anxiety/depression) and including the EQ–Visual Analogue Scale (VAS), on which individuals rate their overall perceived health state (scale of 0 to 100)	Paper survey (pat.)
Quality-Adjusted Life Year (QALY)	Calculate QALY: Generating these requires the HRQL preference weight (obtained from the EQ-5D-5L© value set for Germany EQ-VT v. 2.0) [92] and time in days between HRQL measurements [93]. QALY scores range from 1 (perfect health) to 0 (dead) [94].	Paper survey (pat.)
GvHD	Incidence and grade of chronic and acute GvHD	EHR
Overall survival rate	Overall survival rate from start of study participation	EHR
Conditioning regimen	Treatments used to prepare a patient for stem cell transplantation (e.g., chemotherapy, monoclonal antibody therapy, and radiation to the entire body)	EHR
Donor match/type	Human leukocyte antigen (HLA) tissue type	EHR
Disease	Primary disease	EHR
If death	Date and cause of death	EHR
If relapse	Date of relapse	EHR

*Abbreviations. BAASIS* Basel Assessment of Adherence to immunosuppressive medication scale. *EHR* Electronic Health Record, *EQ-5D-5L*© European Quality of Life 5 Dimensions 5 Level Version, *EQ-VT* EQ valuation protocol, *GvHD* Graft-versus-Host-Disease, *HRQL* health related quality of life, *pat* patient, *PETS* Patient Experiences with Therapy and Self-management, *QALY* quality-adjusted life years

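### GvHD is hypothesised as incidence, but the only inferential method named for it is a GLMM over repeated time points, which does not estimate cumulative incidence

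*Protocol article*

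**What the plan says.** Under Study aims, Aim 1a expects the groups to have "equal medical outcomes (acute and chronic GvHD incidence, overall survival"). Table 3 defines the outcome in the same terms: "Incidence and grade of chronic and acute GvHD", taken from the electronic health record.

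Table 2 lists "Incidence/grade chronic and acute GvHD" with medical record and CRF as source. It marks nine time points, T0b to T8 (days 30, 60, 90, 120, 150, 180, 240, 300 and 365).

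The Analysis section, Aim 1a, covers the group comparison of all secondary outcomes together: "To analyze the target secondary outcomes over the course of time, descriptive analyses will be carried out and GLMM will be used to determine differences". For the primary outcome it adds: "The relevant variables (i.e., time, study group, and group x time interaction) will be entered into the models". One event outcome is taken out of this general rule: "Overall survival will be analysed using the Kaplan-Meier method and the log-rank test". GvHD is not. On incomplete data the section says only: "Multiple imputations will be considered for missing data".

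The Background (The SMILe project) notes that "mortality and re-hospitalisation rates remain substantial, especially in the first year post-alloSCT". Date and cause of death and date of relapse are collected. No GvHD onset date is listed.

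**The concern.** Incidence asks whether, and when, a patient first develops GvHD. Each patient contributes at most one first acute and one first chronic event, and death without GvHD ends the chance of having one. A mixed model over nine time points asks how the odds of a positive record compare between groups across visits. The two questions coincide only under particular rules for coding a visit and for leaving the risk set.

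This matters because of what the intervention is meant to do. The Background describes monitoring that may shorten reaction time when health deteriorates, and it calls for early detection and treatment of complications. Such an intervention could plausibly alter how long GvHD lasts, or when it is recorded, without altering how many patients get it. GvHD and overall survival are the two medical outcomes that the trial expects to be equal. A visit-level result could therefore be read as contradicting equal incidence when incidence is equal, or could obscure a real incidence difference.

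**Working it through.** **1. Is there a figure of the plan's own to reproduce?** No. The article gives no GvHD rate, margin or event count. Incidence, onset, duration and mortality below are assumptions.

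**2. What the model compares under each coding of a visit.**
- *Present at the visit:* prevalence among patients alive. A case with onset at day 100 lasting past day 365 gives six positive records (T3 to T8). A case with onset at day 280 lasting past day 365 gives two (T7, T8). Each is one incident case.
- *Ever so far:* cumulative status, so early onset is weighted more than late onset.
- *New since the last time point:* targets incidence, provided that the patient leaves the risk set after first onset or death.

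The article does not say which applies.

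**3. Size under present-at-visit coding, no deaths.** Assume onset uniform on days 15 to 300 (a span of 285 days) and exponential duration with mean m. For a case, the probability of being positive on visit day v, with b = min(v, 300), is

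p(v) = (m/285) × [exp(−(v − b)/m) − exp(−(v − 15)/m)].

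Summing over the nine days gives the expected positive records per case, R. With incidence 50% in both groups, visit prevalence is 0.5 × R/9.

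| Mean duration | R | Visit prevalence | Odds ratio against 180 days |
|---|---|---|---|
| 180 days | 2.70 | 0.150 | reference |
| 120 days | 2.18 | 0.121 | (0.121/0.879)/(0.150/0.850) = 0.78 |
| 90 days | 1.82 | 0.101 | (0.101/0.899)/(0.150/0.850) = 0.64 |

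The incidence ratio is 1.0 throughout. Changing the common incidence to 30% or 70% moves the odds ratios only to 0.79 or 0.77 (120 days) and 0.65 or 0.62 (90 days).

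**4. Ever-so-far coding, same onset assumption.** Shift onset 15 days earlier in one group. Over the nine visits, the expected cumulative records per case are 1335/285 = 4.68 without the shift and 1440/285 = 5.05 with it. At 50% incidence, prevalence is 0.5 × 4.68/9 = 0.260 against 0.5 × 5.05/9 = 0.281, an odds ratio of 1.11. The number of cases is the same.

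**5. At the trial's size.** Data were simulated at the nine visit days with 40 per group, two-sided 0.05, visits after death dropped, and about 45% of patients in each group ever having GvHD before death (200 to 400 runs, Monte Carlo error about 1 to 3.5 points). A random-intercept logistic GLMM on present-at-visit records rejected as follows:
- equal durations: 6.0% to 6.5%;
- mean duration 120 vs 60 days: 15% to 21%, odds ratio about 0.6;
- mean duration 120 vs 40 days: 30% to 43%, odds ratio about 0.4.

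On the same data, a comparison of ever-GvHD proportions rejected in about 5% to 9% of runs. A GEE on new-since-last-visit records rejected in about 5%.

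**6. Death.** With 40 per group, equal GvHD hazard and equal duration, but one-year mortality of 30% vs 10%, the GLMM on patients alive rejected in 5% to 6% of runs, with odds ratios of 1.04 to 1.08. The share who ever had GvHD before death was about 42% to 43% against 47% to 49%. Dropping visits after death therefore did not by itself create a clear group difference. It does show that the model describes survivors and does not return the cumulative incidence, which moves with mortality.

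**The case against.** The strongest reply is that the article never says how GvHD is coded at a visit. The variable is labelled incidence, so recording new GvHD since the last time point is a natural reading, and step 5 shows that this coding removes the spurious difference. With follow-up ending at onset or death, a binary model over time is a discrete-time cause-specific hazard analysis, which is a legitimate method. Visit coding may also sit in a full protocol or SAP that is not shown.

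Much of this stands, and it rules out several stronger readings that a reader might infer:
- *The GLMM scores persistence.* This is so only under present-at-visit coding, which the text does not specify.
- *Death is treated as missing data, or GvHD is imputed after death.* The text says neither. Multiple imputation is only to be considered, death is not named as missing data, and death dates are collected.
- *Episodes between visits are lost.* The source is the medical record, which can capture them.
- *The rejection rates in step 5 are type I error.* They reflect a real difference in duration. The model is answering another question.

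The descriptive analyses can also report incidence by group whatever model is used.

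What the reply does not remove is the choice that the article does make. It names a longitudinal GLMM for the secondary outcomes, takes overall survival out of that rule, and leaves GvHD in. That is a stated method that does not match a stated hypothesis, and it matches only under rules that are not given.

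**Conclusion.** The point holds as a mismatch between hypothesis and named method. Aim 1a concerns GvHD incidence, while the only inferential method named for GvHD is a GLMM over repeated time points, with no competing event named although first-year mortality is called substantial. If GvHD is coded as present at each visit, equal incidence with unequal duration can give a visit-level odds ratio of about 0.6 to 0.8. That range is illustrative: it rests on assumed incidence, onset and durations, treats GvHD as one condition, and would not arise under new-onset coding. The documents do not show that the trial will code GvHD this way or that it will mishandle deaths. GvHD is a secondary outcome, and the primary analysis and sample size are unaffected. It is worth correcting before analysis because the remedy is cheap and the question is one of the trial's two expected-equal medical outcomes.

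**What to change.** In the Analysis section, except GvHD from the general GLMM statement, as is already done for overall survival, and specify:
- time to first acute GvHD and time to first chronic GvHD, analysed separately, with death without that form of GvHD as the competing event;
- cumulative incidence by group (Aalen-Johansen) with Gray's test, or cause-specific hazards, reported with confidence intervals;
- maximum grade per patient, summarised by group, for acute and chronic GvHD;
- any visit-level GLMM kept only as a description of GvHD prevalence among patients alive, with the visit coding stated.

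Add the date of first onset of acute and of chronic GvHD to the CRF, taken from the medical record.

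The cost is a small amount of extra data entry and analysis. The medical record is already the source for GvHD, and death dates are already collected. No visit or patient questionnaire is added.
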